### Sample size considerations

A modification of the formula for sample size calculation for a MAMS design for binary outcomes [32] was made based on the methodology for CRTs [33] to identify each stage of the trial. We assume that each ANC day will have at least 40 women attending for the first time, 90% will satisfy the eligibility criteria and at least 60% will consent to participate, so having a cluster size of at least 21. We also assume that in the SOC arm 25% of men will satisfy the definition of the primary outcome [34]. For the first stage, six ANC days per arm (36 days in total) would be needed to detect an absolute difference of 15% in linkage compared to 25% in the SOC arm using a FWER of 0.2 with 80% pair-wise power and a coefficient of variation (*k*) of 0.10 [21]. In general, under the stated assumptions the trial has 80% chance of detecting a 1.6-fold increase in testing and linkage within 28 days compared to SOC at 5% significance level. Sample size for the second stage will be re-calculated based on empirical estimates at interim analysis with FWER of 0.1 and 80% power.

Very little clustering within ANC days is expected, hence we have assumed that *k* = 0.10 (intraclass correlation coefficient = 0.003). The simulation study assumed that *k* = 0.2 and differs with the final design in this respect resulting in six and seven clusters per arm in the final design and the simulation, respectively. A larger than conventional (0.05) FWER of 0.2 and 0.1 for stage 1 and stage 2, respectively, may lead to erroneously taking forward an ineffective intervention. However, given that this is a phase II trial this is not a major concern as it guards against dropping interventions that may otherwise prove to be effective in a larger, phase III trial. A more conventional pair-wise power of 0.8 was chosen to ensure that there is a high chance of taking forward most of the efficacious interventions from stage 1.

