### Trial simulation

A simulation study was set up to compute the overall probability of the trial to find at least one intervention whose efficacy is different compared to the SOC arm at the end of stage 2 (minimal power). The simulation was conducted under the alternative hypothesis with an assumed effect of 29–40% versus 25% in the SOC arm (Table 1). Additional key assumptions included that each ANC day (cluster) would have 20 participants with power set at 80% for each stage (Table 1). The simulation showed that at least two interventions would significantly improve the trial primary outcome (Table 2). These interventions would then be further tested in a potential phase III trial.

**Table 1 Tab1:** Simulation inputs

Description	Input
Number of ANC days (clusters) per arm for both stages	6–20
Number of participants per ANC day	20
Linkage to care or prevention for the SOC arm in stages 1 and 2	25%
Linkage to care or prevention for the 5 intervention arms in stages 1 and 2	29–40%
SD of the mean of cluster-level proportions per arm (7 clusters, stage 1)^a^	0.05–0.08

*ANC* antenatal care, *SOC* standard of care, *SD* standard deviation

^a^Computed using *σ* = *k* × *μ* where *σ* is the standard deviation of the true cluster-level proportions; *k* is the coefficient of variation (assumed to be 0.2) and *μ* is the mean of the proportions per arm

Operating characteristics: stage 1 *α* = 0.2; stage 2 *α* = 0.1; 1 − *β* = 0.8

**Table 2 Tab2:** Simulation results

	First stage		Simulations in which arm was dropped at interim^c^	Assumed
Study arm	^a^Proportion	SD^b^	Proportion	Proportion^d^
1 Standard of care	0.250	0.048	NA	0.250
2 Intervention	0.291	0.055	0.441	0.290
3 Intervention	0.299	0.058	0.336	0.300
4 Intervention	0.310	0.059	0.215	0.310
5 Intervention	0.321	0.061	0.114	0.320
6 Intervention	0.400	0.078	0.000	0.400

Exact intervention not specified here as there is no evidence about a particular one of the 5 interventions being investigated

*SD* standard deviation

^a^Proportion of male partners linked to care or prevention

^b^Assumed (0.050, 0.058, 0.060, 0.062, 0.064, 0.080) in arms 1–6, respectively

^c^Scenarios assumed for the 6 trial arms at the start

^d^If *p* value was > 0.2 at interim analysis, discontinued from recruitment

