### Statistical analysis

Analyses will be done in R [35] and Stata 14.0 (Stata Corp., TX, USA). Baseline characteristics will be computed as proportions or median (interquartile range (IQR)), as appropriate, by arm in each of the two stages of the trial. Any variables that show imbalances will be adjusted [33] for when analysing the trial outcomes at the end of the second stage. We will assume that the two stages of the trial are independent [26] and will proceed to carry out a test of the null hypothesis of no difference in effectiveness of each intervention compared to the SOC. We will do this by analysing data from the first stage first followed by interim decisions to drop arms; then we will conduct and analyse data from the second stage (no overlap of participants from the first stage). Analysis of the whole trial will then be based on combined *p* values from both the first stage and the second stage using the weighted inverse normal (WIN) method [36] for arms that are not dropped at interim. A weighted average of the log (risk ratio (RR)) will be computed for the whole trial using estimates from each trial stage. All analyses will be by intention-to-treat taking as the denominator the number of women who were eligible and take into account the clustered design.

Given the small number (six) of clusters per arm in the first stage, analysis will be by cluster-level summaries using mean of proportion of male partners per clinic day who link to care or prevention in each arm [33]. The proportion of male partners who link into care or prevention will be computed per clinic day for each arm with number of men achieving the primary outcome and the number of women eligible and recruited in ANC on enrolment day as denominator. A log transformation of the clinic day proportions will be applied if a positive skew is observed [33]. The geometric mean of clinic day proportions in each of the five intervention arms will be compared to the SOC arm using an unpaired *t* test [33]. An estimate of the RR and a 95% CI will also be computed for each comparison by dividing the geometric mean of proportions in each intervention arm and the geometric mean of proportions in the SOC arm [33].

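### The sample size section claims 80% power for the trial at a 5% significance level, which conflicts with the plan's chosen family-wise levels of 0.2 and 0.1 and does not follow from six clinic days per arm

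*Protocol article*

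**What the plan says.** All references are to the Methods of the Protocol article.

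- **Sample size considerations, stage 1:** six clinic days per arm are to detect 25% against 40% "using a FWER of 0.2 with 80% pair-wise power and a coefficient of variation" of 0.10.
- **Same section, the trial:** "under the stated assumptions the trial has 80% chance of detecting a 1.6-fold increase in testing and linkage within 28 days compared to SOC". The sentence closes with "compared to SOC at 5% significance level". It does not say whether the 5% is per comparison or family-wise, or one- or two-sided.
- **Same section, stage 2:** "Sample size for the second stage will be re-calculated based on empirical estimates at interim analysis with FWER of 0.1 and 80% power".
- **Same section, rationale:** "A larger than conventional (0.05) FWER of 0.2 and 0.1 for stage 1 and stage 2, respectively" is defended as suitable for a phase II trial, because it protects against losing interventions that might work in phase III.
- **Trial simulation, footnote to Table 1:** "stage 1 *α* = 0.2; stage 2 *α* = 0.1".
- **Statistical analysis:** "Analysis of the whole trial will then be based on combined *p* values from both the first stage and the second stage". The method of combination is the weighted inverse normal. No level is given for the combined p value. The same section says "An estimate of the RR and a 95% CI will also be computed for each comparison". Dunnett's test is to control the error rate within each stage, and the only p value set against a threshold is the interim one, at 0.2.

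**The concern.** A section that explains why 0.05 was not used should not describe the trial's performance at 5%. The reader is left with two printed figures that could apply at the end of the trial: 0.1, attached to stage 2, and 5%, attached to the trial as a whole. The end-of-trial result informs which arms may go on to phase III, so the level matters for any arm whose combined p value lies between 0.05 and 0.1.

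The sentence also makes a checkable claim, 80% power at 5%. If that is not what six days per arm deliver, readers are told the design is stronger than it is.

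**Working it through.** **Inputs (Sample size considerations).** p0 = 0.25 and p1 = 0.40, so the ratio is 0.40/0.25 = 1.6, the same contrast as the stage 1 difference of 15 points. Cluster size m = 21 (40 × 0.9 × 0.6 = 21.6). k = 0.10; this agrees with the stated intraclass correlation, since k²p0/(1 − p0) = 0.01 × 0.25/0.75 = 0.0033. Six days per arm. Sidedness is not stated.

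**Formula (standard for cluster trials with proportions).** Days per arm: c = 1 + (z_α + z_β)² × R, where

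R = [p0(1 − p0)/m + p1(1 − p1)/m + k²(p0² + p1²)]/(p1 − p0)²
= [0.1875/21 + 0.24/21 + 0.01 × 0.2225]/0.0225
= 0.02258/0.0225 = 1.0036.

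The added 1 is the small-sample correction. Power with c days is Φ(√[(c − 1)/R] − z_α), or with c in place of c − 1 if the correction is left out.

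**Step 1: reproduce six days.** At an unadjusted two-sided 0.2: 1 + (1.2816 + 0.8416)² × 1.0036 = 5.52, so 6, with power 83%. With k = 0.2 and m = 20, as in the simulation, the same formula gives 7.07, in line with the seven clusters the plan reports there. A second route to six is the one-sided per-comparison level equivalent to a Dunnett family-wise 0.2 over five arms (0.062) without the correction: 5.67. Neither route uses 5%.

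**Step 2: power at 5% with six days.**

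| Reading of 5% | Normal, with +1 | Normal, without +1 | t, 10 df |
|---|---|---|---|
| Two-sided | 61% | 69% | 60% |
| One-sided | 72% | 79% | 74% |

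Two-sided with +1: √(5/1.0036) − 1.96 = 0.272, and Φ = 0.61. Days needed for 80% at two-sided 5%: (1.96 + 0.8416)² × 1.0036 = 7.88, or 8.88 with the correction, so 8 or 9.

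**Step 3: could the sentence mean both stages together?** Stage 2 is not yet sized. With 12 days per arm (two equal stages, assumed), two-sided 5% power is 88% if 2 is subtracted from the days and 91% if 1 is. That is not 80% either.

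**Step 4: does 0.05 or 0.1 matter for the combined p value?** Take stage p values of 0.19 and 0.09, which pass 0.2 and 0.1, with equal weights (assumed). Treated as one-sided: (0.878 + 1.341)/√2 = 1.569, so p = 0.058. This passes at 0.1 and fails at 0.05. Treated as two-sided in the same direction: (1.311 + 1.695)/√2 = 2.126, so p = 0.034, which passes both. Sidedness must therefore be stated along with the level.

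**Step 5: how often?** A two-stage simulation used 4,000 trials per scenario, 21 women per day, k = 0.10, arms kept if the Dunnett p value was at most 0.2 in the favourable direction, and equal weights. The combined p value of the better arm fell between 0.05 and 0.1 in about 2% of trials at a true 40% and about 5% at a true 35%. Six days per arm in stage 2 is an assumption; a larger stage 2 makes both shares smaller.

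**The case against.** **The 5% decides nothing.** It occurs once, in a power statement, and no p value in the article is compared with 0.05. Stage 2 is to be analysed in the same way as stage 1, so the natural reading is that its Dunnett-corrected p values meet 0.1. This stands, and it is why the point is an inconsistency to correct, not a competing decision rule.

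**The 5% may be a rounded per-comparison level.** A Dunnett family-wise 0.2 over five comparisons corresponds to about 0.055 per comparison, two-sided. The article does not say this. At that level six days give about 62% power and 8.63 days are needed, so the 80% would still not follow.

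**The level for the combined p value can be left to the analysis plan.** The article announces a detailed analysis plan. The silence alone is no fault, and this stands. It does not excuse two figures in one section that disagree.

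**Stronger readings that the article does not support.** A reader might infer that the final conclusion has no level at all, that the 95% interval is a third competing level, or that error control is lost because the level will be chosen after the interim. The 95% interval is described alongside an explicit interim cut of 0.2, so it is descriptive. Nothing says the level will be set after the interim. Nor is final selection a mechanical pass or fail: it concerns arms judged promising, and even at the interim the p value is one of three criteria. A larger figure, about 11% of trials between 0.05 and 0.1, arises only for the stage 2 p value taken alone with six days. Success at 0.1 is then 53%, whereas the plan will re-size stage 2 for 80% power; with ten days the share is 5%.

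**Conclusion.** The point holds in a limited form. The 5% phrase contradicts the family-wise levels the plan chose and defended, and its 80% power does not follow from six days per arm: about 60-61% at two-sided 5%, 69% without the small-sample correction, and 79% at best under a one-sided reading that the article does not state. These figures rest on the plan's own inputs and the standard cluster-trial formula.

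Because the whole-trial analysis rests on a combined p value, and 0.1 and 5% are the only printed levels that could apply to it, the conflict should be removed. The expected effect on conclusions is small, about 2% of trials at the design effect and 5% at a true 35%, given equal weights and six days per arm in stage 2. The documents do not show that error control has been lost.

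**What to change.** 1. In the sample size section, delete the 5% phrase. Otherwise restate the sentence as a per-comparison calculation with its sidedness and the power it actually gives (about 60% two-sided with six days per arm, t with 10 df).
2. State before the interim that the combined p value, built from the Dunnett-corrected stage p values, is judged at the 0.1 family-wise level the plan already chose, and give its sidedness.
3. Keep the 95% interval as a descriptive estimate, labelled as not matching the decision level.

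The cost is a few sentences, with no new data or participants. At submission (9 November 2016) the interim was planned for 20 January 2017, so there was time to fix the level first.

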This analysis involves more than two comparisons with a single control arm which can lead to higher than the specified FWER or significance level. Therefore, Dunnett’s test [29] will be applied to the *t*-statistics generated from the unpaired *t* test to control the stage-wise FWER. Final decision-making at interim analysis will compare the Dunnett-corrected *p* values to stage 1 FWER of 0.2. The first of the three-part criteria for dropping trial arms will then be considered after examining final *p* values at the end of the first stage (interim analysis). Although sample size will be re-calculated at the end of stage 1, the total number of clinic days per arm is still presumed to be small for stage 2. Since the two stages are assumed to be independent, cluster-level summaries approach analogous to stage 1 analysis will also be followed in stage 2 comparing intervention arms that proceed to stage 2 with the SOC arm. A detailed analysis plan will be developed to guide analysis of the trial.

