## Trial status

At the time of submission on 9 November 2016, 32 of 36 clusters (total of 800 participants recruited) were covered for the first of the two trial stages. Interim analysis is planned for 20 January 2017. The second stage is planned to run for 4 months; we will compute the required sample size for the second stage at interim analysis to achieve the specified 80% power.

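### The stated 80% power is set stage by stage and is not shown to be the power of the combined-stage test or of the two-stage procedure that gives the trial's conclusion

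*Protocol article*

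**What the plan says.** **Sizing.** Under Sample size considerations, the modified multi-arm multi-stage formula is used "to identify each stage of the trial". Stage 1 has six clinic days per arm at a family-wise error rate (FWER) of 0.2 with 80% pair-wise power. For stage 2: "Sample size for the second stage will be re-calculated based on empirical estimates at interim analysis with FWER of 0.1 and 80% power". Trial simulation works "with power set at 80% for each stage", and Trial status repeats the target: "we will compute the required sample size for the second stage at interim analysis to achieve the specified 80% power".

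**A trial-level claim.** Sample size considerations adds that "under the stated assumptions the trial has 80% chance of detecting a 1.6-fold increase in testing and linkage within 28 days", at a 5% significance level.

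**Decision rule.** Under Statistical analysis, the interim compares Dunnett-corrected p "values to stage 1 FWER of 0.2", and arms above that level are considered for dropping. For arms not dropped, the analysis of the whole trial is based on combined p "values from both the first stage and the second stage using the weighted inverse normal (WIN) method". Dunnett's correction is described as stage-wise. The article prints no level, weights or power for the combined test.

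**The concern.** Three probabilities are in play: the power of the stage-2 comparison alone, the power of the combined test for an arm that reached stage 2, and the chance that an effective arm both passes the interim and succeeds at the end. The article computes the first and then states 80% for the trial. The second should be higher than the first, because a retained arm brings favourable stage-1 evidence with it. If the drop is applied as written, the third cannot exceed the chance of passing the interim, however large stage 2 is.

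At stake is how stage 2 is sized and what readers and the data monitoring board believe 80% refers to. Trial simulation says that overall power at the end of stage 2 was the object of the simulation, but Table 2 reports only first-stage proportions, SDs and interim drop fractions. The article therefore has no figure that could stand in for the missing one.

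**Working it through.** **Inputs (Sample size considerations):** control 0.25; intervention 0.40 (difference 0.15, ratio 0.40/0.25 = 1.6); m = 21 per day; k = 0.10; six stage-1 days per arm; FWER 0.2 then 0.1.

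**Assumed, because not printed:** sidedness (both tried); equal WIN weights; combined p compared with 0.05 or 0.1; two arms kept; WIN applied to Dunnett-adjusted p values.

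**1. Reproduce the plan's figure.** Cluster formula: c = 1 + (z_α + z_β)² × V / 0.15², with V = p0(1−p0)/m + p1(1−p1)/m + k²(p0² + p1²).
- V = 0.1875/21 + 0.24/21 + 0.01 × 0.2225 = 0.00893 + 0.01143 + 0.00223 = 0.02258, and V/0.0225 = 1.0037.
- Two-sided 0.2 without multiplicity: (1.282 + 0.842)² = 4.51, so c = 1 + 4.52 = 5.52, rounded up to 6.
- With k = 0.20: V = 0.02926, c = 6.86, rounded up to 7. Both printed counts reproduce.
- One-sided Dunnett 0.2 (critical value 1.53) without the +1 gives 5.67, rounded up to 6. Two-sided Dunnett 0.2 (critical value 1.92) gives about 7.6, so 8.

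The printed six is therefore a single-stage figure.

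**2. The 80% at 5% statement.** With six days, SE = √(0.02258/6) = 0.0613 and 0.15/0.0613 = 2.445. At two-sided 5%, 2.445 − 1.960 = 0.485, which is 69% power on the normal approximation; the t test gives 60%. The statement does not reproduce for six days per arm.

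**3. Chance of passing the interim.** Two-sided Dunnett: 2.445 − 1.92 = 0.53, or 70%. One-sided: 2.445 − 1.53 = 0.91, or 82%.

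**4. Two-stage rule (normal-approximation simulation).** Stage 2 is sized alone for 80% at Dunnett FWER 0.1 with two arms. WIN statistic: (z1 + z2)/√2, where each z is the normal quantile of the adjusted p. Paired entries are for combined p against 0.05 / 0.1.

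| | Two-sided | One-sided |
|---|---|---|
| Stage-2 days per arm | 8 | 6 |
| Stage-2-alone power | 82% | 81% |
| WIN power, arm retained | 93% / 96% | 94% / 98% |
| Whole trial, drop binding | 65% / 68% | 77% / 80% |

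The last row is the chance of passing times the row above, for example 0.70 × 0.93 = 0.65 and 0.82 × 0.98 = 0.80. With t-based critical values the days become 9 and 7, and the powers at a combined level of 0.1 hardly change (97% and 68%; 98% and 81%).

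**5. If the drop is not binding.** If no arm is ever dropped for its p value, whole-trial power (two-sided, 8 days) is 79% / 85%.

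**6. Effect of more stage-2 days.** Two-sided, drop binding, combined level 0.1: 58–60% at 4 days, 64% at 6 and 68% at 9, against a ceiling of 70%.

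**The case against.** The strongest reply is that a stage-2 test at FWER 0.1 is in the plan. Statistical analysis describes a stage-2 comparison of retained arms with standard of care analogous to stage 1, and the Design section says that analysis of second-stage data may lead to phase III. So 80% at 0.1 can correctly be the power of that comparison. This stands: one should not say that no stage-2 test exists. It does not make 80% the power of the combined test, which the article names as the basis for the whole trial.

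Further, that stage 2 is sized on its own is an inference. The article never says so in those words, and the stage-2 number is not printed. But every sizing statement is by stage, and the printed counts fit a single-stage formula.

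Four stronger readings are tempting and are not supported:
- *The trial is underpowered.* One-sided Dunnett with a combined level of 0.1 gives about 80%. The drop is only to be considered, and cost may justify keeping an arm. The low two-sided figure also partly reflects six days being too few for 80% under two-sided Dunnett, which is a separate stage-1 matter.
- *Stage 2 recruits about twice the days needed.* Four days give 85% for a retained arm (two-sided) only if the combined level is 0.1, which is not printed; at 0.05 they give 77%. The extra days also raise whole-trial power (step 6).
- *Stage-2 size cannot affect whole-trial power.* It can, up to the ceiling set by the interim.
- *Error is inflated.* With a binding drop and a combined level of 0.1, the global-null FWER is about 0.065 one-sided, below 0.1.

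Leaving the WIN weights and level to the announced analysis plan is ordinary for a protocol article and is not criticised here.

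**Conclusion.** The point holds as a mis-stated power. The 80% belongs to the stage-2 comparison alone. It is not shown to be the power of the combined test (about 93–98% for a retained arm) or of the two-stage procedure (about 65–68% two-sided, 77–80% one-sided, with a binding drop). The trial-level sentence uses a third significance level and is not derived from the two-stage rule.

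The ranges rest on the plan's planning values, two arms kept, equal weights, a combined level between 0.05 and 0.1, and a normal approximation. Drops for safety or cost are not modelled. The figures are pair-wise; they are not the chance of finding at least one effective arm. As the article stands, stage 2 has not yet been sized, so the correction should be made before it is.

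**What to change.** In Sample size considerations, keep the re-calculation from interim estimates, but choose the stage-2 days per arm by simulating the rule that decides: interim drop at Dunnett p > 0.2, then the WIN-combined p at the level and weights the sponsor has fixed beforehand. For the chosen number of days, state both the WIN power for a retained arm and the whole-trial power including the drop. Replace the sentence giving the trial an 80% chance at 5% by the whole-trial figure at the level actually used, and bring Trial simulation and Trial status into line.

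Cost: one simulation and a few sentences; the restatement itself needs no extra participants. The stated whole-trial power may come out below 80%. If stage 2 were shortened because the retained-arm figure looks generous, whole-trial power would fall, so the choice of days should rest on the whole-trial figure.
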